## Methods

### Study Design

We will conduct a multicenter, prospective, intervention, single-group study to evaluate the efficacy and safety of direct hemoperfusion using PMX-DHP for patients with COVID-19. Efficacy will be evaluated by the primary end point, which is the rate of Ordinal Scale for Clinical Improvement after PMX-DHP of at least 1 point from a status of 4, 5, or 6 on day 15, based on previous studies for COVID-19 treatment (Table 1) [23]. Further, safety will be confirmed by the incidence of serious adverse events and problems. The effect of PMX-DHP will be estimated by setting a control group with background factors from non–PMX-DHP patients enrolled in the COVID-19 registry at participating facilities. Since this study will carry out PMX-DHP, setting up a sham group is difficult in terms of ethics because the therapy is relatively invasive. As such, this study will be carried out as a single-group open-label study and will be compared with a historical control. The historical control will be selected from the COVID-19 registry according to age, gender, and severity of pneumonia.

**Table 1 table1:** Purpose and end points.

Purpose			End points		Validity and reason for selection of end points

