The following exclusion criteria will be used: severe progression of multiple organ failure; P/F ratio of 100 or below; extracorporeal membrane oxygenation (ECMO); hospitalization for more than 15 days; platelet count of 20,000/μL or less; cytotoxic or biological treatments (anti-interleukin [IL]–1, anti-IL-6 [tocilizumab or sarilumab], T cell or B cell targeted treatment [rituximab, etc], tyrosine kinase inhibitor or interferon) within 4 weeks prior to consent; treatment with tumor necrosis factor inhibitor within 2 weeks prior to consent; treatment with convalescent plasma or intravenous immunoglobulin for COVID-19; and consideration by the principal investigator or subinvestigator to be unfit to participate in this study.

In case of nonparticipation in the study, administration of remdesivir, dexamethasone, and tocilizumab will be considered if indicated and not already administered. Furthermore, systemic management including oxygen therapy will be performed for deterioration of respiratory function.

A schematic illustration of the study design is presented in Figure S1 in Multimedia Appendix 1.

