### Statistical Analysis

The main purpose of this study is to verify the efficacy in PMX-DHP cases compared to the control in the COVID-19 registry for the primary end point. Particularly, the efficacy of PMX-DHP will be evaluated by comparing the improvement rate (decrease) of 1 point or more from status 4, 5, or 6 on day 15 based on the eight-category evaluation with the COVID-19 registry.

Not hospitalized with resumption of normal activitiesNot hospitalized but unable to resume normal activitiesHospitalized not requiring supplemental oxygenHospitalized requiring supplemental oxygenHospitalized requiring nasal high-flow oxygen therapy, noninvasive mechanical ventilation, or bothRequiring invasive mechanical ventilationRequiring ECMODeath

The status and the percentage of PMX-DHP cases at each evaluation time will be calculated, and the number and percentage of people whose day 15 status improved by 1 or more points from day 1 will be calculated. Furthermore, the following analysis will be planned for comparison with control cases.

Bias is included when comparing the rate of improvement of control cases for 15 days from the time of hospitalization against cases that underwent PMX-DHP several days after hospitalization. Therefore, the number of days from hospitalization to the date of PMX-DHP administration will be calculated for each case.

The effect of PMX-DHP will be estimated using the propensity score based on the data, which integrates this study and the registry. The propensity score will be created based on age, gender, body temperature, etc, and analysis methods such as matching will be used. A significance level on both sides of 5% will be used.

The following results will be calculated for cases enrolled in this study:

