Pathological improvement rate on day 15 (status 1, 2, and 3 in the eight categories) from the start of PMX. The number and percentage of people who reached status 1, 2, and 3 on day 15 at a 95% CI will be calculated. Furthermore, the same items will be calculated on day 29.P/F improvement on day 4 and 8. The descriptive statistics of P/F on day 1, day 4, and day 8 will be calculated and presented on a transition chart.Changes in cytokines, coagulation markers, and urinary biomarkers. The descriptive statistics of clinical laboratory test values that take continuous values will be calculated. For laboratory findings, which are classification variables, the number and proportions at each level will be calculated at each point in time.Invasive mechanical ventilation avoidance rate and duration of use. The number and proportion of people who underwent invasive mechanical ventilation between day 15 and 29 will be calculated.ECMO avoidance rate and duration of use. The number and proportion of people who underwent ECMO between day 15 and 29 will be calculated.

Similar to the primary end point, the efficacy of PMX will be evaluated for the aforementioned secondary end points using propensity scores based on data integrated with the enrolled cases in the registry.

The safety end point is the incidence and rate of adverse events. Multiplicity will not be adjusted in the analysis of safety end points. In the estimation of the ratio to the number of cases and presence or absence of occurrence, an exact 95% CI for the binomial distribution will be calculated for each group.

In addition to clinical laboratory items, continuous quantity data will be tabulated by group through descriptive statistics, while classification variables will be tabulated through the number of people or rate, among other appropriate methods.

Furthermore, PMX malfunctions will also be tabulated. Subgroup analysis will be performed by status and age at the time of enrollment.

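### The plan names a time-zero bias in its registry comparison, but only calculates each case's delay; it fixes no aligned control start and gives the delay no use

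*Protocol article*

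**What the plan says.** The study has a single arm, and its efficacy comparison rests on registry controls. The Statistical Analysis section raises the timing problem itself: "Bias is included when comparing the rate of improvement of control cases for 15 days from the time of hospitalization", set against "cases that underwent PMX-DHP several days after hospitalization". The response follows at once: "Therefore, the number of days from hospitalization to the date of PMX-DHP administration will be calculated for each case". The article says nothing further about that number.

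For PMX cases, the primary result is the "number and percentage of people whose day 15 status improved by 1 or more points from day 1 will be calculated". The article does not define day 1 for this endpoint, but a secondary endpoint shows what day 15 means: "Pathological improvement rate on day 15 (status 1, 2, and 3 in the eight categories) from the start of PMX".

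Controls are chosen as stated under Study Design: "The historical control will be selected from the COVID-19 registry according to age, gender, and severity of pneumonia". For the score, Statistical Analysis says: "The propensity score will be created based on age, gender, body temperature, etc, and analysis methods such as matching will be used". Neither list names hospital day. The eligibility criteria exclude only "hospitalization for more than 15 days", so a case may be enrolled well into the stay.

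**The concern.** A case's 15-day window opens at PMX start. The only window the article mentions for a control opens at admission. Three things follow if the text is carried out as written.

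- **Selection before time zero.** A case must still be in hospital, at status 4 to 6 and off ECMO on the later day when PMX starts. Patients who improved and left early are gone, which lowers the case rate. Patients who died or went onto ECMO early are also gone, which raises it.
- **Different baselines.** Improvement is measured from day 1. A patient who goes from status 4 to 5 before PMX counts as improved on returning to 4. A control with the same course, scored from admission, must reach 3.
- **Different stage of illness at assessment.** A case's day 15 falls later in the hospital stay than a control's.

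At stake is the primary comparison. There is no randomized group to fall back on, so a distortion from timing would be read as a treatment effect or would hide one.

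**Working it through.** **1. The two clocks side by side**

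| | PMX case | Registry control |
|---|---|---|
| Time zero | PMX start, several days after admission | Admission is the only origin mentioned |
| Condition at time zero | Still hospitalized, status 4-6, off ECMO on that later day | Status 4-6 implied by the endpoint; day not fixed |
| Assessment | Day 15 from PMX start | 15 days from hospitalization |
| Use of the delay | Calculated | None stated |

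With the longest permitted delay, a case's day 15 falls near hospital day 15 + 15 = 30, against hospital day 15 for a control.

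**2. Could the open covariate list absorb the delay?** No. Days from admission to PMX do not exist for an untreated control until that control is given an index day, and none is defined. Covariates measured at two different stages of illness do not align the start of follow-up either.

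**3. Does the mismatch have a known sign?** Assume that 55% of controls improve by hospital day 15 (the planning rate in Sample Size Estimation) and that cases are those not yet improved at PMX start. The following are constructed examples.

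- Constant hazard from admission: h = -ln(0.45)/15 = 0.0532. From any later start, the 15-day rate is 1 - exp(-15 × 0.0532) = 55%. The bias is nil.
- No improvement for 5 days, then a constant hazard, with PMX on day 5: h = -ln(0.45)/10 = 0.0799. The rate is 1 - exp(-15 × 0.0799) = 69.8%. An ineffective treatment gains about 15 points.
- Half of the improvers improve by day 5, so 1 - 0.275 = 0.725 remain: the rate is 1 - (0.45/0.725)^1.5 = 51.1%. An ineffective treatment loses about 4 points.

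The sign depends on the course of improvement by hospital day, which the document does not give.

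**4. The plan's own power figures.** A two-proportion z-test with pooled null variance and continuity correction 0.5(1/n1 + 1/n2), two-sided 10%, 82.5% against 55%, gives 65.3%, 78.2% and 83.4% for 30, 60 and 90 controls. The plan states 65%, 78% and 83%. Its figures for control rates of 50% and 60% also reproduce within 1 point. None of them allows for different time zeros.

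**5. What an assumed shift would do.** The inputs are 30 cases, 30/60/90 controls, a control rate of 55% and two-sided 5% (the level in Statistical Analysis). The test is a pooled z without continuity correction:

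P = Φ((d - 1.96 × SE0)/SE1), where d is the difference in rates, SE0 the pooled and SE1 the unpooled standard error.

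Example with no true effect, a shift of +10 points and 30 controls: d = 0.10, SE0 = √(0.60 × 0.40 × 2/30) = 0.1265, SE1 = √(0.65 × 0.35/30 + 0.55 × 0.45/30) = 0.1258. P = Φ(-1.175) = 12.0%.

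| Shift in the PMX rate | Quantity | 30 controls | 60 | 90 |
|---|---|---|---|---|
| 0 | False positive favouring PMX | 2.5% | 2.5% | 2.5% |
| +5 points | same | 5.8% | 6.4% | 6.7% |
| +10 points | same | 12.0% | 14.2% | 15.3% |
| 0 | Power, ratio 1.5 | 63.8% | 75.4% | 80.4% |
| -5 points | same | 45.2% | 55.1% | 59.9% |
| -10 points | same | 28.8% | 35.4% | 38.7% |

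**The case against.** The strongest reply is that the article does not adopt the admission-based comparison. It describes that comparison as biased and then introduces a response. The delay is exactly the quantity needed to give controls an index day, so alignment may have been intended and the sentence left unfinished. The covariate list and the matching method are both left open, and index-date rules often sit in a full protocol or SAP that is not shown. This stands as a limit on wording: one can say that the article fixes no aligned control time zero and no use of the delay, but not that the final analysis will count controls from admission. It does not remove the point. The article raises the bias and states its response, and that response on its own corrects nothing.

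Three stronger readings are tempting, and the document does not support them.

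- *Controls pass no condition at time zero.* The comparison is defined from status 4, 5 or 6, so controls are alive and off ECMO, and they are selected on severity. What differs is that cases stayed eligible until a later hospital day.
- *Controls spend their first days worsening, so PMX is favoured.* The Introduction's remark that severity develops at about one week counts from symptom onset, not admission. No interval from onset to admission is given.
- *The delay is typically long.* Fifteen days is the outer limit. The text speaks of several days, and the requirement of a positive test within one week shortens the delay for patients tested at or after admission, unless they were retested.

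**Conclusion.** The point holds in this form. The plan recognises a time-zero bias in its primary comparison, states a response that does not correct it, and gives neither an aligned start for controls nor a use for the calculated delay. This should be settled before the comparison is run.

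A reader might infer that the result is bound to favour PMX, or by how much. The document supports neither: it gives no delay distribution and no improvement rates by hospital day. The bias could run either way and is nil under a constant improvement hazard from admission. The 10-point figures (false positives favouring PMX rising from 2.5% to about 12-15%, or power falling from about 64-80% to 29-39%) rest on an assumed shift, a 55% control rate and an unadjusted z-test rather than the planned propensity analysis. They show how sensitive a comparison of this size is; they do not estimate the actual bias.

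**What to change.** State the control time zero and use the delay to set it:

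- Give each control an index day equal to the hospital day on which its matched case started PMX.
- Require the control to be hospitalized, at status 4 to 6 and otherwise eligible on that day.
- Match on status and on the propensity covariates as measured on that day.
- Score improvement from the index-day status 15 days after the index day, using the same day count as for cases.
- Keep any admission-based comparison as a sensitivity analysis only.

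The cost is analysis-plan wording and some programming, with no new patients. The control pool becomes somewhat smaller. The method also depends on the registry holding status near the index day and 15 days later. Where only some days are recorded, the rule for taking the nearest value should be written down in advance.

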SARS-CoV-2 was identified as the causative virus of an unknown pneumonia (COVID-19) that emerged in Wuhan City, Hubei Province, China in December 2019. Depending on the case, the condition become severe about 1 week after onset, and respiratory failure rapidly develops, requiring intensive care management [17]. Patients may have markedly impaired oxygenation early in the course of the disease, which is said to be due to increased activity of the coagulation system; plasminogen activator inhibitor-1 expression is increased in older adults and in people with hypertension, obesity, and diabetes, which are risk factors for COVID-19; and in severe cases of COVID-19, STAT3 and plasminogen activator inhibitor-1 activation is escalated, leading to catastrophic consequences. A characteristic of COVID-19–related severe pneumonia cases is ground-glass opacities rapidly progressing in both lungs visible in chest computed tomography findings [18]. With subsequent progression toward severity, these opacities turn into infiltrative shadows [19]. This condition could be classified as DAD [20]. According to the analysis results of 191 COVID-19 cases in Wuhan, 100% of nonsurviving cases have sepsis while 93% have acute respiratory distress syndrome. The three most relevant risk factors in the early stage were age, Sequential Organ Failure Assessment score, and 1 μg/mL or higher D-dimer [21]. As for the congealing fibrinogenolysis system, according to a different report, D-dimer, fibrin and fibrinogen degradation product, and prolonged prothrombin time were significant factors in nonsurviving COVID-19 cases, suggesting that the effects of the congealing fibrinogenolysis system are associated with the aggravation of pneumonia [22]. As of February 2021, clinical trials and clinical studies are being conducted with several existing treatments, but except for remdesivir and dexamethasone, no drugs or treatments have yet been approved by the Japanese regulatory authorities.

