**Secondary**					
	To evaluate the efficacy and safety of PMX-DHP	Pathological improvement rate (status 1, 2, and 3 in the aforementioned eight categories) from the start of PMX^b^. PaO2/FiO2 improvement on day 4 and day 8 Changes in cytokines, coagulation markers, and urinary biomarkers Occurrence of serious adverse events and problems Invasive mechanical ventilation avoidance rate and duration of use ECMO^c^ avoidance rate and duration of use Mortality rate		Evaluation of respiratory function, safety, and efficacy of PMX-DHP	

^a^PMX-DHP: polymyxin B-immobilized fiber column direct hemoperfusion.

^b^PMX: polymyxin B-immobilized fiber column.

^c^ECMO: extracorporeal membrane oxygenation.

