### Dosage

While administering an anticoagulant drug (nafamostat mesilate: approximately 30-40 mg/hr or heparin approximately 40-60 U/kg one shot + approximately 40-60 U/kg/h), 1 Toraymyxin at a flow rate of 60-120 mL per minute should be administered for 3-6 hours (maximum of 24 hours), and at least 2 doses (maximum 3) should be used. The follow-up will be carried out up to 4 weeks after the end of PMX-DHP. PMX-DHP does not have to be conducted in consecutive days, but the interval between each session must be as short as possible.

The equipment operation for direct hemoperfusion will go as follows (Multimedia Appendix 3):

Prepare the extracorporeal circulation device (blood pump, anticoagulant infusion pump, monitoring of arterial and venous pressure of the inlet and outlet pressure of this product)Precautions before use (inspection of exterior, confirmation of sterilization)Cleaning and primingCirculation:
Insert a double lumen catheter into the patient’s femoral vein or internal jugular vein to serve as the site for blood access

Using a blood pump, perform whole blood hemoperfusion at a flow rate of 60-120 mL per minute, which will be determined according to the patient’s condition

When using this product, anticoagulants (nafamostat mesylate, heparin) are administered by continuous infusion from the blood circuit on the blood removal side.

Duration of extracorporeal circulation is 3 to 24 hours per piece

The maximum working pressure of this product is 66 kPa (500 mHg). Note that the pressure difference between the inlet and outlet of this product may increase due to internal clogging caused by the formation of blood clots.

Heparin or nafamostat will be used in the anticoagulant therapy to be performed for direct hemoperfusion associated with PMX-DHP. Moreover, since the target patients of this treatment are within the scope of heparin and nafamostat, the anticoagulation treatment is not considered as the target treatment of this study.

There are no restrictions on the antiviral treatment for COVID-19; however, in principle, the antiviral treatment will not be changed during the study period.

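### The avoidance end points for invasive ventilation and ECMO count only days 15 to 29, so support that begins and ends before day 15 is missed

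*Protocol article*

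**What the plan says.** Table 1 of the protocol article lists "Invasive mechanical ventilation avoidance rate and duration of use" among the secondary end points, with a matching entry for ECMO. It attaches no time window to either.

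The Statistical Analysis section supplies the window. For ventilation: "The number and proportion of people who underwent invasive mechanical ventilation between day 15 and 29 will be calculated". For ECMO: "The number and proportion of people who underwent ECMO between day 15 and 29 will be calculated". It then says that the efficacy of PMX on the secondary end points will be judged with propensity scores on data integrated with the registry, as for the primary end point.

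The time origin is day 1. The primary analysis reports that "the number and percentage of people whose day 15 status improved by 1 or more points from day 1 will be calculated", and the status 1 to 3 end point on day 15 is timed from the start of PMX.

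**The concern.** An avoidance end point should count the event from the moment the treatment could prevent it. Here the count opens two weeks after that moment. A patient intubated on day 2 and extubated by day 12, or dead by then, has no ventilation on days 15 to 29 and is not counted as having undergone it.

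The protocol's own account puts the relevant period earlier. Its aim is to stop progression from moderate to severe disease, and it describes that progression as fast. Because these end points also feed the registry comparison, the window decides which events contribute to an efficacy statement and not merely to a descriptive table.

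**Working it through.** **No figure to reproduce.** The article gives no expected ventilation or ECMO rate. Its only design figures are the power values for the primary end point, which do not depend on this window.

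**Day count.** Days 15 to 29 inclusive are 29 − 15 + 1 = 15 days. Days 1 to 14 are the other 14 of 29.

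**What the protocol places in days 1 to 14**

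| Item | Where | Text |
|---|---|---|
| Treatment sessions (at least 2, at most 3) | Dosage | "the interval between each session must be as short as possible" |
| Oxygenation | Statistical Analysis | "The descriptive statistics of P/F on day 1, day 4, and day 8 will be calculated" |
| Course of the disease | Introduction | "the condition become severe about 1 week after onset, and respiratory failure rapidly develops" |

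The third row runs from symptom onset, not from PMX, so it does not fix a study day. Patients must, however, have a positive test within the past week and already be hypoxaemic at entry. It is therefore reasonable to expect much of the further deterioration before day 15. That is an inference, not a figure in the article.

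**What each reading of the two sentences captures**

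| Course after day 1 | In use on any of days 15–29 | Started on days 15–29 | Cumulative from day 1 to day 29 |
|---|---|---|---|
| Started and ended before day 15 | no | no | yes |
| Started before day 15, still in use on day 15 | yes | no | yes |
| Started on day 15 or later | yes | yes | yes |

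The first row is lost under either literal reading. The second is lost only under the narrower one.

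**Can size or direction be stated?** Only under assumptions, and these counts are invented for illustration. Of 30 patients, 24 enter unventilated and 6 enter ventilated. Of the 24, 6 are intubated by day 14 (3 of them off ventilation or dead before day 15), and 1 more is intubated later.

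- Ever ventilated among the 24: 6 + 1 = 7, so avoidance is 17/24 = 71%.
- Ventilated on days 15–29 among the 24: 3 + 1 = 4, so avoidance is 20/24 = 83%.
- Started on days 15–29 among the 24: 1, so avoidance is 23/24 = 96%.
- Ventilated on days 15–29 among all 30, with none of the 6 still ventilated on day 15: 26/30 = 87%.
- The same with all 6 still ventilated: 30 − 4 − 6 = 20, so 20/30 = 67%.

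Against 71%, the literal window gives 67% to 96%, depending on a denominator and a reading that the article does not state. The shift can go either way.

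**The case against.** The strongest reply is that this is a slip of wording. The same section reports the status 1 to 3 end point on day 15 and repeats it on day 29, so the authors may have meant counts up to each of those days. That is plausible, but the text does not say it. If it is what was meant, both sentences still misstate the end point.

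Second, early events are not invisible elsewhere. The article says "The status and the percentage of PMX-DHP cases at each evaluation time will be calculated", mortality is a separate secondary end point, and duration of use carries no window. This stands in part. However, status at set times is a snapshot that can miss support between assessments, and none of these is an avoidance rate.

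A reader might also infer more than the documents support:

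- *That all events of the first two weeks are lost.* Patients intubated early and still ventilated on day 15 fall in the window if use, rather than start, is counted.
- *That patients ventilated at entry are in the denominator, or that death without support counts as success.* The article states neither. It speaks only of a proportion of people, and an article may leave such detail to the full protocol.
- *That the avoidance rate is too high in both groups.* The illustration shows that this does not follow if patients ventilated at entry are included.

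**Conclusion.** The point holds in a limited form. The window is a rule the article states, not a detail it omits. Followed as written, it leaves out ventilation or ECMO that began and ended before day 15, in a study whose treatment and oxygenation readings fall in that period and whose aim is to prevent progression. Unless the registry analysis defines its own window, the propensity-score contrast inherits the gap.

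The size and direction of the bias cannot be derived from the article, and the percentages above rest on assumed counts. The conclusion takes day 1 as the start of PMX, which the primary and day 15 analyses imply.

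Two secondary end points are affected. The primary end point and its power figures are not. Severity: should-fix.

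**What to change.** Reword the two sentences along these lines:

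- *Ventilation:* among patients at status 4 or 5 on day 1, the number and proportion who started invasive ventilation from the start of PMX (day 1) up to day 15, and up to day 29.
- *ECMO:* the same two cumulative counts among all patients. ECMO at entry is an exclusion criterion, so everyone enrolled is at risk.
- *Death:* show deaths without the support beside each count, so that they are not read as avoidance. A composite with death or a competing-event analysis would each do. The choice matters less than stating it.
- *Controls:* apply the same windows from each control's index day.

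The cost is small. The ventilation denominator loses patients already ventilated on day 1. Start dates of support must be available in both the study data and the registry. Duration of use suggests that the study records them, but the article does not say so for either source, and this should be confirmed before the wording is fixed.

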### Sample Size Estimation

In this study, the efficacy of PMX-DHP will be evaluated by comparing the improvement rate (decrease) of 1 point or more from status 4, 5, or 6 on day 15 based on the eight-category evaluation with the COVID-19 registry. In a paper that reported on the compassionate use of remdisivir for COVID-19 cases [23], of 51 cases who were under invasive ventilation, noninvasive oxygen support, or low flow oxygen (corresponds to the status 4, 5, and 6 in this study), improvement by at least 1 stage was noted in 34 cases (approximately 57%; median follow-up period: 18 days). Further, in a randomized clinical trial investigating the effect of lopinavir-ritonivar on COVID-19 about 38% (75/199) of cases recovered (improved by 2 points or more on a 6-point scale) 14 days after randomization [24]. Based on the aforementioned, we assume that approximately 50% to 60% of non–PMX-DHP COVID-19 cases will improve by 1 point. On the other hand, although there is insufficient data on the expected effects of PMX-DHP, we can consider PMX-DHP effective if the improvement rate of cases in this study is 1.5 times that of the non–PMX-DHP cases.

We set a 2-sided type I error at 10%. When the improvement rate of non–PMX-DHP cases is approximately 55%; if there are 30 cases in this study; and the control group is set at 30, 60, and 90 cases, the detection power would be approximately 65%, 78%, and 83%, respectively. Similarly, if the improvement rate of non–PMX-DHP cases is approximately 50%, the detection power would be 54%, 67%, and 72%, respectively. If the improvement rate is approximately 60%, the detection power would be 78%, 90%, and 94%, respectively. However, when compared with control cases, the detection power fluctuates due to the adjustment in the confounding factor.

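### The invasive-ventilation and ECMO avoidance rates have no death component, yet they are used to judge efficacy against the registry

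*Protocol article*

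**What the plan says.** Table 1 of the protocol article lists as a secondary end point "Invasive mechanical ventilation avoidance rate and duration of use", gives the same pair for ECMO, and lists mortality as a separate item.

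The Statistical Analysis section then says how the pairs are computed. For ventilation: "The number and proportion of people who underwent invasive mechanical ventilation between day 15 and 29 will be calculated". For ECMO: "ECMO avoidance rate and duration of use. The number and proportion of people who underwent ECMO between day 15 and 29 will be calculated". No denominator is given for either. Duration appears only as a label, with no formula, population or rule for death.

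The next sentence turns the list into efficacy comparisons: "Similar to the primary end point, the efficacy of PMX will be evaluated for the aforementioned secondary end points using propensity scores", on data pooled with the registry. The list it follows has five items: reaching status 1, 2 or 3 (day 15 and day 29), P/F ratio, laboratory markers, invasive ventilation, and ECMO. Mortality is not among them.

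The same section sets out the eight-category scale, with death as the worst category, below ECMO. Eligibility Criteria and Recruitment admits patients already on invasive ventilation and excludes patients on ECMO. On follow-up, the Dosage section says: "The follow-up will be carried out up to 4 weeks after the end of PMX-DHP".

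**The concern.** An avoidance rate is meant to show that fewer patients came to need support. Death precludes later support, so a count of receipt alone cannot tell recovery without support from death without it. The day 15 to 29 window adds a second gap: nobody who dies before day 15 can receive support inside it, even if they died on a ventilator or on ECMO.

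This would matter less if the rates were purely descriptive. They are used to evaluate efficacy in an open-label, non-randomised comparison with registry patients, and nothing in the design makes death without support, or death before day 15, equally frequent in the two groups. A group with more such deaths could show the better avoidance rate, and that could be read as benefit. It would also reverse the ordering of the trial's own scale, on which death is worse than either form of support.

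**Working it through.** **The plan's own figures.** The document gives no expected rate of ventilation, ECMO or death, so there is no figure on this point to reproduce. Its only design figures are the powers for the primary end point. At a 55% control rate these reproduce (65.3%, 78.2% and 83.4% against the stated 65%, 78% and 83%) with a pooled, continuity-corrected two-proportion z-test at two-sided 10%. The present point does not depend on them.

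**Inputs from the document.** N = 30 treated patients (Sample Size Estimation); counting window day 15 to 29 (Statistical Analysis); death = status 8.

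**Reading 1: all enrolled patients as denominator.** Let u be the number who received the support in the window. The avoidance rate is A = (N − u)/N.
- A death without support in place of a counted supported case lowers u by 1 and raises A by 1/30 = 3.3 points. For 3 such deaths the rise is 3/30 = 10 points; for 1 to 5 deaths it is 3.3 to 16.7 points.
- Compared with surviving unsupported, dying unsupported leaves u and A unchanged. The rate does not register the death.

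**Reading 2: patients alive at day 15 as denominator.** If k patients die unsupported before day 15, they leave the denominator and A = (N − k − u)/(N − k).

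**Illustration (assumed numbers).** Suppose 6 of 30 patients deteriorate enough to need support. Of these, k die without it before day 15, and the other 6 − k receive it in the window, so u = 6 − k.

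| k | Reading 1 | Reading 2 | Alive and free of support, at most |
|---|---|---|---|
| 0 | 24/30 = 80% | 24/30 = 80% | 24/30 = 80% |
| 3 | 27/30 = 90% | 24/27 = 88.9% | 24/30 = 80% |
| 6 | 30/30 = 100% | 24/24 = 100% | 24/30 = 80% |

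The last column assumes that the other 24 patients survive unsupported. If instead all 6 were ventilated and died before day 15, u = 0 and both readings again give 100%. Unsupported deaths after day 15 stay in the denominator on either reading and count as avoided.

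**Baseline support.** ECMO is an exclusion criterion, so all 30 can in principle avoid it. For ventilation, patients ventilated at entry cannot. If, say, 10 of the 30 were, each death among the remaining 20 would weigh 1/20 = 5.0 points.

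**If the window wording is loose.** Should the intent be cumulative use up to day 15 and up to day 29, deaths on support would be counted, but deaths without support would still fall in the complement.

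**Duration.** Take 10 ventilated patients, 5 who die and 5 who are extubated after 14 days, and compare mean raw days when three deaths become recoveries at 14 days.
- Deaths at 5 days: (5×5 + 5×14)/10 = 9.5 becomes (2×5 + 8×14)/10 = 12.2, so saving lives looks 2.7 days worse.
- Deaths at 20 days: (5×20 + 5×14)/10 = 17.0 becomes (2×20 + 8×14)/10 = 15.2, so it looks 1.8 days better.

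The direction depends on when deaths occur, which the document does not give.

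**The case against.** The strongest reply is that the document nowhere says a death is scored as avoidance. It states a count of people who received support and leaves the denominator open; on the day-15-survivor reading, early deaths are dropped, not credited. This stands as a limit on the wording. It does not rescue the end point, because conditioning on survival does not make death a failure either.

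Second, a condensed article may leave the handling of death to the full protocol or analysis plan. For duration this holds: only a label is given, so its silence is no defect in itself. For avoidance it does not, because the article states the calculation and that calculation omits death.

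Third, deaths are visible elsewhere. The primary end point counts death as failure. So does reaching status 1, 2 or 3 on day 15 and day 29, which sits in the same registry-compared list. Table 1 lists mortality. A reader might infer that nothing offsets the problem; that would be wrong. Still, other end points that show deaths do not correct an avoidance rate that ignores them.

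Fourth, a reader might infer that limits on escalation differ between trial and registry patients. The document gives no basis for that. What can be said is that nothing ensures equality.

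**Conclusion.** The point holds for the two avoidance rates. Followed as written, they ignore death as a competing event while serving as efficacy comparisons with a non-randomised control. The size is 3.3 points per death in place of a counted supported case, assuming all 30 patients form the denominator. The total effect cannot be estimated from the document, and the 80% to 100% range above is an illustration. Neither the primary end point nor any stated design figure changes.

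A stronger reading is tempting: that death improves both avoidance and duration. The document does not support it. Dying unsupported looks better only against receiving support, not against surviving without it. Duration has no stated formula, and raw days can move either way.

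Mortality is absent from the list just before the registry-comparison sentence. The word *aforementioned* could be read as reaching back to Table 1, so its omission from the comparison is probable but not certain.

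**What to change.** - **Avoidance.** Define success as alive and free of invasive ventilation from day 1 through day 29, and separately for ECMO, among patients not already on that support at baseline. State the denominator. Show the components (death without support, support, and both) beside the composite.
- **Mortality.** Name day-29 mortality explicitly in the registry comparison.
- **Duration.** If it is to be compared with the registry, use support-free days to day 29 with death scored worst, where the registry data allow. Otherwise report raw duration descriptively only. A competing-risk analysis is a reasonable alternative.

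**Cost.** For trial patients the change should be mainly one of wording: death is a category of the scale, day-29 status is already analysed, and the stated follow-up extends to about that point. It is not necessarily wording only for the controls. The registry must hold support and death data through day 29, and the document does not show that it does; this should be confirmed first. The other cost is that a composite must always be shown with its components.
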